## Methods

### Study Design and Setting

This study is funded by the National Heart, Lung, and Blood Institute under a K23 award designated Independent Clinical Trials Not Allowed (K23HL161328), reflecting the determination by the National Institutes of Health that the proposed research does not constitute an independent clinical trial. Aim 1 is an observational cohort study, and aim 2 is a feasibility pilot intended to inform a future randomized controlled trial. Accordingly, this study was not registered on ClinicalTrials.gov. This study includes 3 aims with different designs, and we selected a reporting guideline for each. We follow the STROBE (Strengthening the Reporting of Observational Studies in Epidemiology) guideline for the aim 1 cohort [28], the TIDieR (Template for Intervention Description and Replication) for the aim 2 SCCCD intervention [29], and the COREQ (Consolidated Criteria for Reporting Qualitative Research) for the aim 3 interviews [30]. We report the protocol following the SPIRIT (Standard Protocol Items: Recommendations for Interventional Trials) 2025 statement [31]. Completed TIDieR and SPIRIT 2025 checklists are provided as Checklists 1 and 2, respectively.

Participants are recruited through Washington University School of Medicine and the Sickle Cell Clinic at St. Louis Children’s Hospital (SLCH), a regional hub for pediatric SCD care that follows over 400 children and receives approximately 25 newborns with SCD annually. For aim 1, we will recruit 100 children, 50 with SCD and 50 demographically matched peers, who will complete developmental evaluations at 9, 18, and 30 months with concurrent caregiver surveys. For aim 2, an additional 25 children with SCD will be recruited to participate in a 12-month home-visiting intervention. Caregivers of children enrolled in aim 2 may also be invited to participate in a qualitative interview as part of aim 3.

### Participants

#### Aim 1: Incidence Cohort (n=100)

Children with SCD (n=50) under 9 months of age with all SCD genotypes and their caregivers will be recruited from the Sickle Cell Clinic at SLCH. Children without SCD (n=50) will be recruited as a comparison cohort and matched at the group level to the SCD cohort on the distributions of age, sex, race, socioeconomic status, and Area Deprivation Index [32], rather than paired individually. Group-level matching will be finalized after enrollment. Typically developing children will be recruited through SLCH general medicine, community early childhood centers, local pediatricians, public libraries, local early intervention providers, and faith-based organizations, using methods previously successful in this lab [33,34]. Children will be excluded if they have a diagnosis associated with developmental delay that is not attributable to SCD, or if the family is not English-speaking.

Caregivers of children with SCD will be approached by phone or following a regularly scheduled clinic visit. Interested caregivers will review the informed consent document with a member of the research team by phone, Health Insurance Portability and Accountability Act (HIPAA)–secure video call, or in person.

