Despite the high prevalence of developmental delay in this population, critical gaps remain. No study has prospectively characterized developmental trajectories across the first 3 years of life in children with SCD using a demographically matched comparison cohort and psychometrically robust assessment methods. Earlier work suggests that delays may worsen as children age [6,7,27], but this trajectory has not been rigorously evaluated. Additionally, no disease-specific intervention has been formally tested for infants and toddlers with SCD, and little is understood about the contextual factors that would support broader implementation of such a program. Because known environmental mediators of development—including socioeconomic status and disease severity—require comparison to well-matched peers, a prospective design with a demographically balanced comparison cohort is essential.

The purpose of this study is to determine the incidence and severity of developmental delays at 9, 18, and 30 months of age in children with SCD compared to demographically matched peers (aim 1); evaluate the effect of a 12-month, home-based SCCCD intervention on developmental outcomes in children with SCD (aim 2); and identify contextual determinants that facilitate or impede caregiver participation in developmental screening and home-based intervention, in preparation for future broader implementation (aim 3).

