#### Aim 2: Intervention Cohort (n=25)

An additional 25 infants with SCD under 9 months of age will be recruited for the SCCCD intervention following the same inclusion and exclusion criteria as aim 1. Following the 9-month baseline evaluation, consenting families will participate in the 12-month SCCCD program.

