### Measures

All outcome measures are summarized in Table 1. Demographic information will be collected from all participants at enrollment, including caregiver age, education, health literacy, marital status, household income, racial or ethnic identity, and number of children in the household. Clinical information collected for children with SCD will include SCD genotype, insurance status, hospitalizations and treatments, disease-modifying medication use, and neuroimaging results if available.

**Table 1. T1:** Summary of outcome measures.

Measure	Purpose	Type	Time point (months)	Aim
Bayley-4^a^	Child development	Clinician administered	9, 18, and 30	1 and 2
ASQ-3^b^	Child development	Caregiver report	9, 18, and 30	1 and 2
ITACS^c^	Child participation in family routines	Caregiver report	9, 18, and 30	1 and 2
BRIEF-P^d^	Executive functioning	Caregiver report	30 only	1 and 2
HOME^e^ Inventory	Home environment	Clinician observation	9, 18, and 30	2
PROMIS^f^ Depression (8 items)	Caregiver mental health	Caregiver report	9, 18, and 30	1 and 2
Semistructured interview	Implementation determinants	Interview	Ongoing	3

a Bayley-4: Bayley Scales of Infant Development, Fourth Edition.

b ASQ-3: Ages and Stages Questionnaires, Third Edition.

c ITACS: Infant Toddler Activity Card Sort.

d BRIEF-P: Behavior Rating Inventory of Executive Function-Preschool.

e HOME: Infant Toddler Home Observation for Measurement of the Environment.

f PROMIS: Patient-Reported Outcomes Measurement Information System.

The Bayley Scales of Infant Development, Fourth Edition (Bayley-4) is the primary outcome measure and has been the gold standard for evaluating and identifying developmental delay in children for over 50 years [25]. The Bayley-4 is completed in 45 to 60 minutes and evaluates 5 developmental domains: cognition, fine motor, gross motor, receptive language, and expressive language. Raw scores are converted to scaled scores, where a score of 10 indicates performance at the 50th percentile. A score greater than 1 SD below the mean will be classified as a developmental delay.

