### Data Analysis

#### Aim 1

Evaluations will be scored according to their respective manuals. Mixed effects regression will be used to analyze developmental outcome data, with time, group, and time-by-group interaction entered as fixed effects. This approach accounts for within-subject and within-group variability across the 3 longitudinal time points. Scores from the Bayley-4 will be compared to the ASQ-3. Covariates will include race, age, sex, caregiver education, socioeconomic status, disease-modifying medication use, and therapeutic intervention received. The number of evaluations completed and any therapeutic or behavioral interventions received (eg, physical therapy, OT, speech-language therapy) will be documented. Children who receive therapy services during the study period will be analyzed separately.

#### Aim 2

Standardized scores will be calculated for each assessment according to the respective manuals. Scores greater than 1 SD below the mean will be classified as a developmental delay. Repeated measures ANOVA will be used to compare group mean scores at 9, 18, and 30 months. Logistic regression will compare the number of children classified with a delay at 30 months to the aim 1 cohort. The number of caregivers approached and enrolled will be documented, and visits scheduled and completed, along with topics from visit notes, will be summarized. Additional analyses will examine possible changes in the home environment and caregiver mental health before and after the intervention. When the outcome is binary, a mixed effects logistic regression will be used, with time, group, and time-by-group interaction entered as fixed effects and variation of subject intercept as a random effect. Time will also be tested as a random effect in a more elaborate model.

#### Aim 3

Two research team members will use an iterative inductive and deductive thematic analysis approach to review all transcripts and generate themes for a preliminary codebook [60]. The preliminary codes will be applied to 4 interviews using NVivo software; any deviations will be discussed, and the revised codebook will be applied to all remaining interviews [62]. Codes will be analyzed for themes, and participation data from aim 2 will be summarized and integrated with qualitative findings [63,64].

The study protocol and deidentified data will be made available from the corresponding author on request and consistent with the NIH Data Management and Sharing Plan.

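### The aim 2 comparison of delay at 30 months states no adjustment for SCD genotype, although genotype is collected and both SCD cohorts admit every genotype

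*Protocol article*

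**What the plan says.** All references are to the protocol article.

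- **Eligibility.** Participants, Aim 1: "Children with SCD (n=50) under 9 months of age with all SCD genotypes and their caregivers will be recruited from the Sickle Cell Clinic at" the study hospital. The Aim 2 part of the same section applies those criteria again: "An additional 25 infants with SCD under 9 months of age will be recruited for the SCCCD intervention following the same inclusion and exclusion criteria". Both SCD cohorts are therefore open to every genotype.
- **Matching.** The children without SCD are "matched at the group level to the SCD cohort on the distributions of age, sex, race, socioeconomic status, and Area Deprivation Index". This ties the peers to the aim 1 SCD children. Nothing ties the aim 2 children to the aim 1 SCD children.
- **Data collected.** Measures: "Clinical information collected for children with SCD will include SCD genotype, insurance status, hospitalizations and treatments", among other items.
- **Aim 1 analysis.** Data Analysis, Aim 1: "Covariates will include race, age, sex, caregiver education, socioeconomic status, disease-modifying medication use, and therapeutic intervention received". Genotype is not on the list.
- **Aim 2 analysis.** Data Analysis, Aim 2 specifies a logistic regression of delay status at 30 months against the aim 1 cohort and lists no covariates. It does not say whether that cohort means the 50 SCD children or all 100 children. The mixed effects logistic model in the same section has only time, group and their interaction as fixed effects.
- **Background.** The Introduction counts disease severity among the known influences on development: "Because known environmental mediators of development—including socioeconomic status and disease severity—require comparison to well-matched peers".
- **Limitations.** The article concedes that aim 2 has no randomized comparison and may suffer selection bias. It names neither genotype nor severity, and gives no remedy.

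**The concern.** Aim 2 is called a feasibility pilot in Study Design and Setting. The Introduction nevertheless sets it the task of evaluating the intervention's effect, and the Conclusions make the results the foundation for a randomized trial. The 30-month contrast is thus likely to be read as a first estimate of effect.

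That contrast compares children whose families took up a year of home visits with children enrolled in a separate observational cohort. If severity influences development, as the Introduction holds, and genotype carries information on severity, a cohort with fewer severe genotypes would show less delay even with no intervention effect.

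Genotype suits adjustment because it is fixed before baseline and the intervention cannot alter it. The nearest variable in the stated plan, disease-modifying medication use, is listed for aim 1 only. It can change during follow-up, and the intervention's SCD education covers medication adherence, so the intervention might itself affect it.

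**Working it through.** The article gives no alpha, power, effect size or sample-size derivation for this contrast, so there is no figure to reproduce. The check is how far genotype could move the result.

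**Inputs from the article:** 25 aim 2 children; 50 aim 1 SCD children (taking these as the comparator); delay rate 50% in SCD children over 12 months of age (Introduction, earlier work).

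**Assumed inputs, not in the article:** 60% severe genotypes in the comparator; a delay gap of 10 to 30 points between severe and milder classes; two-sided alpha 0.05.

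**1. Sampling error of the contrast.** SE = √[p(1−p)(1/25 + 1/50)] = √(0.25 × 0.06) = 0.122, about 12 points.

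**2. Bias from a systematic difference in mix.** Shift = (difference in share of severe genotypes) × (delay gap).

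- 0.15 × 0.15 = 0.0225, about 2 points, or 2.25/12.2 = 0.18 of the SE.
- 0.20 × 0.25 = 0.05, 5 points, or 5/12.2 = 0.41 of the SE.

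Over a wider grid, with no true effect, 50% delay in the comparator and fewer severe genotypes in aim 2:

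| Delay gap | Difference in mix | Spurious reduction | Odds ratio | Chance of a nominally significant result |
|---|---|---|---|---|
| 10 points | 10 points | 1 point | 0.96 | 5.1% |
| 20 points | 20 points | 4 points | 0.85 | 6.2% |
| 30 points | 30 points | 9 points | 0.69 | 11.2% |

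Without any difference in mix the last column would be 5%.

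**3. Chance imbalance, kept separate.** If both cohorts come from one population, the SD of the difference in severe share is √(0.6 × 0.4 × 0.06) = 0.12, and the probability of a difference of 10 points or more is about 40%. This is not bias, because the unadjusted SE already contains it. With a 20-point gap and 60% severe, 50% delay overall means 58% and 38% in the two classes (0.6 × 0.58 + 0.4 × 0.38 = 0.50). The variance splits as follows:

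- within classes: 0.6 × 0.58 × 0.42 + 0.4 × 0.38 × 0.62 = 0.2404
- between classes: 0.6 × 0.4 × 0.20² = 0.0096
- total: 0.25, the value used in step 1

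Removing the between-class part would lower the SE only from 12.2 to √(0.2404 × 0.06) = 0.120, 12.0 points. Precision is therefore no reason to adjust. Protection against a systematic difference is.

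**The case against.** **The covariate list belongs to aim 1.** A reader might infer that the aim 1 model is wrong to omit genotype. The article does not support that. The model contrasts SCD children with peers, among whom SCD genotype does not vary, so it can be neither matched on nor adjusted for as an ordinary confounder. This objection stands.

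**The Introduction's sentence on severity justifies the peer cohort.** It argues for a demographically balanced comparison group, not for balancing severity between the two SCD cohorts. This also stands. The sentence serves here only as the protocol's own statement that severity matters for development. The article does not say that genotype determines severity.

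**Severity-driven enrollment is not shown.** The two aim 2 withdrawals reported were for moving or for distance. The Intervention section expects missed visits for SCD-related health reasons but allows delivery to run to 15 to 18 months so that dosage is equivalent. Selection by severity is possible under a non-randomized design, but it is not demonstrated.

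**Selection bias is disclosed, aim 2 is a pilot, and an analysis plan may add covariates.** These points lower the stakes. They do not remove the point: the between-cohort test is specified without adjustment, its comparator is loosely named, and a suitable baseline covariate is already being recorded.

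**Conclusion.** The point holds as a cheap improvement to one stated comparison, the aim 2 logistic regression at 30 months. It is not an error in the aim 1 analysis or in the all-genotype eligibility criterion.

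A systematic difference in genotype mix would bias the contrast invisibly. On assumed inputs (15 to 20 point difference in mix, 15 to 25 point delay gap) the shift is about 2 to 5 points, below the standard error of about 12. The wider grid gives 1 to 9 points. All of this rests on assumption, since the article gives neither the share of severe genotypes nor delay rates by genotype.

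A reader might conclude that severity is likely to drive the aim 2 result, or that the chance-imbalance figures measure confounding. Neither follows: the shift is smaller than the sampling error in every scenario shown, and chance imbalance is already reflected in that error.

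**What to change.** In Data Analysis, Aim 2:

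1. State that the comparator for the 30-month logistic regression is the aim 1 SCD children, not the whole aim 1 cohort of 100.
2. Define two genotype classes before the outcome data are examined.
3. Include the class as a baseline covariate in that regression.
4. Tabulate genotype class by cohort.

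The aim 1 covariate list and the eligibility criteria can stay as they are. Reporting aim 1 delay by class, and watching the class split over the 20 aim 2 children still to be recruited, are optional.

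The cost is a change of analysis wording, with no new data, and one extra binary term in a small model. At the assumed 60% severe share, aim 2 would have about 25 × 0.4 = 10 children in the milder class, fewer after attrition, so a penalized fit may be needed if cells are sparse. The adjusted odds ratio is conditional on class, so it should be shown beside the unadjusted one and labeled as such.

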## Results

A total of 128 caregivers have been approached, and 72 have consented. Of those, 13 participants withdrew because of time constraints, interest, or loss to follow-up. As of May 31, 2026, a total of 26 unique participants with SCD have participated in aim 1, and 24 unique participants participated in the comparison cohort. For aim 2 with the pilot intervention, 13 caregivers have been approached and 7 have consented, and 5 caregiver or child dyads have been enrolled and have participated. Two caregivers withdrew due to moving out of state or living outside of the intervention radius (>60 miles). Characteristics of participants to date are available in Tables 2 and 3. Enrollment data can be seen in Table 4.

**Table 2. T2:** Caregiver demographics.

Demographics	Sickle cell cohort (aim 1; n=26)	Typically developing cohort (aim 1; n=24)	Sickle cell cohort (aim 2; n=5)
Parental role			
Mother, n	23	22	5
Father, n	3	2	0
Age (y), mean (SD)	30.9 (7.4)	33.4 (5.0)	28.8 (7.9)
Age group (y), n			
20‐29	17	6	2
30‐39	5	15	3
40‐49	4	3	0

**Table 3. T3:** Child demographics.

Demographics	Sickle cell cohort (aim 1), n	Typically developing cohort^a^ (aim 1), n	Sickle cell cohort (aim 2), n
Gender			
Male	13	13	3
Female	13	11	2
Race or ethnicity			
White	0	15	0
Black or African American	25	7	5
Asian	0	1	0
More than one race	1	1	0
Hispanic	0	2	0
Area of Deprivation Index state values			
1‐4 (least deprived)	6	14	1
5‐7	6	5	2
8‐10 (most deprived)	14	4	2

a One participant is excluded in Area Deprivation Index due to being suppressed in the calculation. Values reflect interim enrollment.

**Table 4. T4:** Current study participant enrollment (May 31, 2026).

Enrollment	Sickle cell disease (aim 1)	Typically developing (aim 1)	Sickle cell disease (aim 2)
9 months	12	10	5
18 months	22	15	0
30 months	18	16	0
Total unique participants	26	24	5
Total approach	84	44	13
Total consent	35	37	7

Participants in aim 1 for the SCD cohort all identify as Black or African American; 7 participants in the comparison cohort identify as Black or African American, 15 identify as White, 1 identifies as Asian, and 1 identifies as more than one race.

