Aim 1 enrollment is ongoing; 50 participants are needed to fulfill the recruitment goal of aim 1 (n=100), 24 more in the SCD cohort, and 26 more in the comparison cohort. Enrollment in aim 2 began in July 2025, and 20 more participants will be recruited to this pilot intervention. As of May 31, 2026, one participant has initiated and completed 5 home visits.

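### Aim 1's comparison cohort can no longer be matched on race at 50 versus 50, deprivation balance needs targeted recruitment now, and the deprivation index is not an adjustment covariate

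*Protocol article*

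**What the plan says.** The Study Design and Setting section sets the target for aim 1: "we will recruit 100 children, 50 with SCD and 50 demographically matched peers". The Aim 1 participants section says the comparison children will be "matched at the group level to the SCD cohort on the distributions of age, sex, race, socioeconomic status, and Area Deprivation Index", without individual pairing, and then adds "Group-level matching will be finalized after enrollment". The Introduction calls a demographically balanced comparison cohort essential, and the Discussion still describes the cohort as matched.

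The Results section reports progress to 31 May 2026: "a total of 26 unique participants with SCD have participated in aim 1, and 24 unique participants participated in the comparison cohort". On race it reports that "7 participants in the comparison cohort identify as Black or African American, 15 identify as White, 1 identifies as Asian"; Table 3 puts the one remaining comparison child under more than one race. The places still to fill are "24 more in the SCD cohort, and 26 more in the comparison cohort". No quota or priority rule is given for them.

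The Aim 1 analysis paragraph begins its covariate list as follows: "Covariates will include race, age, sex, caregiver education, socioeconomic status". It then names disease-modifying medication and therapeutic intervention received. ADI is not in the list, although the participants section names it as a matching factor alongside socioeconomic status.

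**The concern.** The contrast between SCD and comparison children is the main result of aim 1, and its interpretation rests on the two groups being alike in social background. The article's own background section names household income and caregiver education as contributors to delay. If the groups end enrollment far apart on race and neighbourhood deprivation, a difference in Bayley-4 scores or delay rates cannot be read cleanly as an effect of disease.

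The timing makes this worse. Matching is left until recruitment has ended, when the places that could have restored balance have been used. By then scores will also exist. Table 4 already lists 10, 15 and 16 comparison children at 9, 18 and 30 months, and the Procedures section has a written score report prepared after each evaluation. A decision at that stage about which children form the comparison cohort could be made with outcomes in view.

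**Working it through.** **Inputs (Results text, Tables 3 and 4).** SCD: 26 enrolled, 25 Black and 1 of more than one race. Comparison: 24 enrolled, 7 Black, 15 White, 1 Asian, 1 of more than one race. ADI bands 1-4 / 5-7 / 8-10: SCD 6 / 6 / 14 (n = 26); comparison 14 / 5 / 4 (n = 23, one value suppressed). The text says all SCD children identify as Black, whereas Table 3 gives 25 plus 1; this does not affect the conclusion.

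**The plan's own figure.** Remaining recruitment is 50 − 26 = 24 SCD and 50 − 24 = 26 comparison, 50 in total. This agrees with the article.

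**Race, best case at 50 per group.**
- Comparison: (7 + 26)/50 = 66%, or (8 + 26)/50 = 68% if the multiracial child is counted as Black.
- SCD: 25/26 = 96% now, and (25 + 24)/50 = 98% if the next 24 are all Black.
- The gap is therefore about 30 points (96% vs 66%) to 32 points (98% vs 66%), or 28 points if 68% is used against 96%.
- With all 17 non-Black comparison children kept, a Black share t needs 17/(1 − t) children: 17/(1/26) = 442 for 96%, and 17/0.10 = 170 for 90%.
- Equality at 66% from the SCD side would need 33 − 25 = 8 Black children among the next 24. The Introduction says SCD occurs predominantly in Black or African American individuals, so this is not realistic.

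**Standardized differences**, (p₁ − p₂)/√{[p₁(1 − p₁) + p₂(1 − p₂)]/2}:
- Race now, 0.962 vs 0.292: 1.92.
- Race in the best case: 0.83 (25/26 vs 33/50) to 0.92 (49/50 vs 33/50).
- ADI 8-10 now, 14/26 = 0.538 vs 4/23 = 0.174: 0.82.

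**ADI, what balance requires.** The SCD share of 14/26 applied to 49 or 50 comparison children gives 26.4 or 26.9. Subtracting the 4 already enrolled leaves about 22 to 23 of the next 26. Band 1-4 cannot fall below 14/50 = 28%, against 6/26 = 23% in SCD. At the current mix the cohort would end with about 4/23 × 49 ≈ 9 children in band 8-10.

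**What race adjustment costs.** For a linear model with group and a Black/non-Black indicator, the variance of the group effect is inflated by VIF = 1/(1 − r²), where r is the correlation between the two.

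| Scenario (Black/other) | r | VIF |
|---|---|---|
| Now: 25/1 vs 7/17 | 0.70 | 1.95 |
| 50 per group, current mix: 48/2 vs 15/35 | 0.68 | 1.88 |
| 50 per group, all 26 Black: 49/1 vs 33/17 | 0.42 | 1.21 |

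At the current mix, 50 per group is worth about 50/1.88 ≈ 27.

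**Where the adjusted estimate comes from.** In this model each race stratum contributes in proportion to n₁n₂/(n₁ + n₂). Now, Black children give 25 × 7/32 = 5.47 and the others 1 × 17/18 = 0.94, so Black children carry 5.47/6.41 = 85%. In the best case the figures are 49 × 33/82 = 19.72 and 0.94, or 95%. The adjusted comparison therefore rests almost wholly on the Black comparison children: 7 now, 33 at most.

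**The case against.** The strongest reply is that Table 3 is labelled interim, half of aim 1 is still to be recruited, race is already a covariate, and the matching procedure may be set out in a fuller plan. The interim label does not help on race, because 66% is a best case at full enrollment. The covariate does help, and with full targeting its precision cost is modest (VIF about 1.2). What remains is thin overlap if recruitment continues as it has. It is also fair that the Introduction's sentence on balance cites socioeconomic status and disease severity as its reasons, not race; race enters as a matching factor in the participants section.

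Four stronger readings are tempting and are not supported.

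- A reader might infer that finalizing the match can only mean dropping comparison children after their scores are known. The article does not say so. Enrolling beyond 50 or weighting are also possible, and selection on demographics alone is not selection on outcome. Deferral leaves this risk open; it does not establish it.
- A reader might infer that ADI is beyond repair. It is not: the excess in band 1-4 would be 28% against 23%, and band 8-10 can be matched with targeting.
- A reader might infer that leaving ADI out of the model leaves its imbalance wholly uncorrected. Socioeconomic status and caregiver education are covariates and will take up part of it.
- The recruitment sources include "public libraries, local early intervention providers, and faith-based organizations", and a reader might infer that early intervention providers contaminate the comparison cohort with delayed children. The article does not say that the children recruited are those providers' clients and gives no count by source. It excludes children with a diagnosis linked to delay not attributable to SCD, and it analyses children who receive therapy separately. No size can be put on this from the document.

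**Conclusion.** The concern holds. On the stated counts, race matching at 50 versus 50 is out of reach if enrolled children are kept: at most 66% to 68% Black in the comparison cohort against about 96% to 98% in SCD. Dropping non-Black comparison children would restore the match but leave at most 33 or 34 of 50. Deprivation is far off now (54% vs 17% in deciles 8-10) and repairable only with deliberate targeting, for which the article states no rule. ADI is a stated matching factor with no place in the model. The Limitations section mentions none of this.

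The race bound is arithmetic and assumes only that enrolled children stay in and that future SCD enrollment resembles enrollment so far. The variance figures assume a simple linear model with one binary race indicator; the planned mixed model with further covariates will differ somewhat, so they are a guide to size.

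**What to change.** 1. Replace the deferred matching with a rule that applies from now: prioritize the remaining 26 comparison places by race and ADI, using baseline data only. Both targets fall on the same 26 places, so they need to be set together.
2. Add ADI to the aim 1 covariates.
3. Keep all enrolled comparison children in the main adjusted analysis, and pre-state a sensitivity analysis restricted to Black children.
4. Describe the cohort as a covariate-adjusted comparison and not as matched, report standardized differences for each matching factor, and add the imbalance to the Limitations.

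The cost is possibly slower comparison recruitment and giving up the matched label. Even full targeting leaves a race gap of about 30 points at 50 per group, so items 3 and 4 are needed whatever recruitment achieves.
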